## **Methods: data collection, management, and analysis**

### **Data collection instruments**

#### Source documents

Study data are collected on source documents. The PI is responsible for assuring that collected data are complete and accurate. Source documentation (the point of initial recording of a piece of data) supports data collected on the eCRF. Source documents include all recordings of observations or notations of clinical activities and all reports and records necessary for the evaluation and reconstruction of the clinical study. Completed eCRF data are entered into the database within a week of the patient visit being completed.

#### Data collection and study report form monitoring

All data obtained from this study are entered into a local regulation compliant Data Management System [for reference ex: 21 CFR Part 11 (USA)]. This is provided by the Service of Biometry & Clinical Trial Center (CTC) of the I.R.C.C.S. Policlinico San Matteo Foundation (Pavia, Italy). Data are recorded with an Electronic Data Capture (EDC) system using eCRFs. Specifically, the EDC is

based on the RedCap platform. REDCap is a novel workflow methodology and software tool that expedites the electronic collection of research data from a single site or multi-site clinical research study. The software supports a secure web-based application for developing fully functional case report forms (CRFs) and surveys. In particular, through RedCap we implement: (a) Full user authentication (log-on/password) to restrict users to study functions; (b) Real-time data validation, integrity checks for insuring data quality; (c) De-identification options to be applied to data exports to remove fields that contain notes and other information that could identify patient; (d) Centralized, secure storage of research data with back-ups; (e) The study database will be resident on a server in a secure location within the I.R.C.C.S. Policlinico San Matteo Foundation, Pavia, Italy.

The PIs will ensure the accuracy and completeness of the data reported to the DMC. All data entry, modification or deletion is recorded automatically in an electronic audit trail. The PIs will retain all copies of the eCRF in the relevant sections of their Investigator Site File with any required anonymised background information from the medical records as required.

## **Data management**

All the consents of the enrolled patients and a copy of the discharge letters are stored in a safe site in each participating institution, where they will be available to the PIs for data monitoring and analysis. The reviewers will conduct their task in the same site where data are stored.

Once assessed each telephone interview, they fill out the paper sheet for score assignment and then transfer all data to the eCRF.

## **Statistical methods**

A full data management plan and a full statistical analysis plan (SAP) has been revised and approved by the scientific board prior to study start. The SAP does not include details of data on rate of adverse events and decision rules for arm(s) or study termination, as this is not appropriate to this study. After SAP signature by the scientific board (i.e. prior to any statistical analysis), the study database will be locked. Any changes to the protocol-specified or SAP-specified planned analyses that are made after the database lock will be described in the clinical study report.

## ***Analysis strategy***

The main analysis will be performed with an ITT perspective, considering patients lost to follow-up as having score zero.

A secondary analysis will be performed “on treatment”, i.e. on patients who have been reached at the follow-up call.

A sensitivity analysis will also be performed, considering patients lost to follow-up as “average” knowledge (inputting the missing score with mean score across both groups).

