### **Outcomes**

The main outcome will be patients' comprehension of the domains directly related to the video contents, i.e., knowledge of the *diagnosis* and its potential *complication*, corresponding to interview's questions 1-3-4 (see the attached file *Telephone Interview*).

Secondary outcomes will be the knowledge of the prescribed therapy and patients' satisfaction (see the attached file *Telephone Interview*).

The outcomes will be measured through a telephone interview, consisting of a set of questions specifically designed for the purposes of this study (see the attached file "*Telephone interview*"). The interview is made of six questions, focusing on the different domains of comprehension.

The telephone interview is conducted by one of the two researchers responsible for this task. Audio files are then stored on a computer and subsequently reexamined by both reviewers, who will assign a score to each question contained in the interview (see the attached file "*Telephone interview*").

We developed a scheme to aid the reviewers in the interpretation of patients' answers, to reduce reviewers' inter-operator variability (see the attached file *Interpretation of patients' answers*).

Patients' answers will receive a score on a 4-point Likert scale (ranging from zero to three) from low to high knowledge.

Scores from the two independent reviewers will be summed to obtain an overall score. The score for the main outcomes will therefore range: 0-18 for the main outcome (questions 1-3-4), 0-6 for the knowledge of the prescribed therapy (question 2), 0-12 for patient's satisfaction (questions 5-6).

To the best of our knowledge, no currently available validated questionnaires would serve for the purpose of our study, i.e., for the simultaneous measurement of different domains of comprehension across two different medical conditions.

Hence, we have developed the ad-hoc interview and its related interpretation scheme using face and content validity. Construct validation would require an amount of time and resources equivalent to that of the trial itself, pushing it beyond practical feasibility.

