## **Participants timeline**

Patient enrolment will take place in the emergency departments without any time restriction, including night shifts and festivities. Nevertheless, it is possible that the enrolment of eligible patients does not occur in a continuous fashion, as not all the doctors serving in the department participate in the study.

Prior to the discharge of eligible patients, the SIs will invite patients (or caregivers) to participate to the study, explaining its purpose and the methods used. Patients (or caregivers) willing to participate will sign the consent, provide a valid telephone number and are assigned to the study or control group. After patient's discharge, the SIs will transmit the telephone number to the PIs in charge of conducting interviews.

Telephone interviews will be carried out within 48 hours from discharge, using an institutional telephone station located in the emergency department of the IRCCS Fondazione Policlinico San Matteo Hospital.

The telephone station is connected to the institutional computer situated in the same room, which is provided with a free downloadable software for phone call management. All recordings will be stored on the same computer and each file is named with a progressive number code.

The equipment used to carry out phone interviews are situated in the same room where all files related to the study will be stored (consents, discharge letters, opaque envelopes for randomization).

Interviewers will try to contact patients (or caregivers) telephonically with a maximum of five attempts, after which the patients will be considered lost to follow-up.

During a patient's permanence within the emergency department, the SIs do not anticipate to the patient the content of the telephone interview, in order not to influence their answers.

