## **Sample size**

We hypothesize a median score for the primary outcome to be 10 points in the control group, whereas we expect a 20% higher score in the intervention group as suggested by current literature, with standard deviation 4 and non-normal distribution. Group sample sizes of 64 and 64 achieve 80% power to detect this difference with alpha error 5% using a two-sided Mann-Whitney test assuming that the actual distribution is uniform. (Note: this number represents the total number of patients with either DVT or AF, within each study group, since we do not expect differences in the effect by diagnosis).

Since we expect the number of patients lost to follow-up to be 10%, we plan to enroll 72 patients in each group (144 patients in total).

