### Secondary Analyses

Per-protocol analysis for the primary outcome “Knowledge of the medical condition and its main complication”

Two-sample t test with equal variances

| Group                               | Obs | Mean                   | Std. err. | Std. dev.            | [95% conf. interval] |           |
|-------------------------------------|-----|------------------------|-----------|----------------------|----------------------|-----------|
| Standard                            | 69  | 6.130435               | .4200399  | 3.489114             | 5.292258             | 6.968611  |
| Video                               | 68  | 8.779412               | .4795399  | 3.954388             | 7.822246             | 9.736577  |
| Combined                            | 137 | 7.445255               | .3369858  | 3.944318             | 6.778846             | 8.111665  |
| diff                                |     | -2.648977              | .6369054  |                      | -3.90858             | -1.389374 |
| diff = mean(Standard) - mean(Video) |     |                        |           | t =                  | -4.1591              |           |
| H0: diff = 0                        |     |                        |           | Degrees of freedom = | 135                  |           |
| Ha: diff < 0                        |     | Ha: diff != 0          |           | Ha: diff > 0         |                      |           |
| Pr(T < t) = 0.0000                  |     | Pr( T  >  t ) = 0.0001 |           | Pr(T > t) = 1.0000   |                      |           |

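### Scoring unreached patients as zero in the main analysis contradicts the sample-size allowance for loss and, at the protocol's own 10% loss, leaves power near 61–65% instead of 80%

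*Protocol*

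**What the plan says.** The main rule is in Analysis strategy: "The main analysis will be performed with an ITT perspective, considering patients lost to follow-up as having score zero". Participants timeline defines loss by telephone contact alone: interviewers try "with a maximum of five attempts, after which the patients will be considered lost to follow-up".

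Zero is also an obtainable score. The Outcomes section gives a range of "0-18 for the main outcome (questions 1-3-4"), summed over two raters who each score 0 to 3. A zero therefore means that both raters gave the lowest mark on all three questions.

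Analysis strategy adds two companion analyses. One is "on patients who have been reached at the follow-up call"; the other fills missing scores with the mean of both groups. Both rank below the main analysis.

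The planning values are in Sample size: "We hypothesize a median score for the primary outcome to be 10 points in the control group", "we expect a 20% higher score in the intervention group", and "standard deviation 4 and non-normal distribution". The result is 64 per arm for 80% power with a two-sided 5% Mann-Whitney test, raised to 72 per arm for an expected 10% loss.

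**The concern.** Five unanswered calls carry no information about what a patient understood. Entering them as zero records a failed contact as complete ignorance. Analysis by allocated arm does not require this; it is an imputation choice.

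Two consequences follow. First, Sample size and Analysis strategy treat lost patients in incompatible ways. Dividing 64 by 0.9 restores the planned number only if lost patients drop out of the analysis. If they stay as zeros, they shrink the difference and widen the spread, and the stated power does not apply to the main test. Second, because the zeros depend on contact, a difference between arms in contact rates would enter the estimate directly as a difference in knowledge, in either direction.

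**Working it through.** **Inputs.** From Sample size: control score 10 (a median, used here as the mean), difference 20% of 10 = 2, SD 4, two-sided alpha 5%, 64 per arm, 10% loss, 72 per arm. From Supplementary Data 5: reached patients 69 control (mean 6.130, SD 3.489) and 68 video (mean 8.779, SD 3.954), with 72 per arm in the sensitivity analyses. Loss rates by arm are not in the Protocol; those in step 4 are assumptions.

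**1. The plan's own figure.** The normal formula for a difference of 2 with SD 4 gives 63 per arm; the t test gives 63.8, so 64. The Mann-Whitney test has efficiency 1 relative to the t test for a uniform distribution, so 64 stands, and 64/0.9 = 71.1, so 72. The figure reproduces. Direct simulation of the Mann-Whitney test on uniform data at 64 per arm gives about 76%, so the fair comparator below is the simulated power in reached patients.

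**2. Main analysis with loss d = 10% in both arms, scored zero.**
- Expected difference = (1−d)μ₁ − (1−d)μ₀ = 0.9×12 − 0.9×10 = 1.8.
- Variance per arm = (1−d)SD² + d(1−d)μ². Control: 14.4 + 0.09×100 = 23.40 (SD 4.84). Video: 14.4 + 0.09×144 = 27.36 (SD 5.23). Average 25.38, SD 5.04.
- SE at 72 per arm = 5.04×√(2/72) = 0.840; 1.8/0.840 = 2.14; power = Φ(2.14 − 1.96) ≈ 57%.
- By the same formula, 80% power needs 2×(1.96 + 0.84)²×25.38/1.8² ≈ 123 per arm.

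**3. Simulation of the same case** (72 per arm, 10% loss in each, uniform scores, or normal scores rounded and clipped to 0–18):

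| Analysis | Mann-Whitney | t test |
|---|---|---|
| Lost patients scored zero | about 61–65% | about 55% (54–57%) |
| Reached patients only | about 76–79% | about 80–81% |

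Clipping at 18 brings the zero-scored difference to about 1.7 in the normal case. With no true effect and equal 10% loss, the rejection rate is about 5% under the zero rule.

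**4. Unequal loss (assumed rates).** With no true effect the zero rule shifts the estimate by (d₀ − d₁)×10.

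| Loss, control v video | Shift towards video | Type I error, Mann-Whitney |
|---|---|---|
| 10% v 10% | 0 | about 5% |
| 10% v 5% | 0.5 | about 8% |
| 15% v 5% | 1.0 | about 17–18% |
| 10% v 0% | 1.0 | about 17–18% |

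The reverse case, with a true difference of 2 and loss of 5% control v 15% video, gives 0.85×12 − 0.95×10 = 0.7 and Mann-Whitney power of about 22–25%. Here the rule hides a benefit.

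**5. Appended data.** Loss was 72 − 69 = 3 (4.2%) in control and 72 − 68 = 4 (5.6%) in video. Adding those zeros:
- Control 69×6.130/72 = 5.875 (SD 3.63); video 68×8.779/72 = 8.292 (SD 4.34).
- Difference 2.42; SE = √((3.63² + 4.34²)/72) = 0.667; t = 3.62; p = 0.0004.
- Reached patients as printed: 2.65, SE 0.637, t = 4.16. Pooled-mean imputation as printed: 2.52, t = 4.15, which the same reconstruction reproduces.

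**The case against.** The strongest reply is that Analysis strategy already brackets the zero rule with a reached-patient analysis and a pooled-mean analysis, so dependence on the rule would be visible. That stands, and it makes the repair largely a matter of reordering. It does not cure the problem: the primary conclusion and the power statement attach to the zero-scored analysis. Pooled-mean imputation also pulls the arms together and understates the variance.

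A second reply is that equal loss makes the rule conservative for a superiority claim. This is right about error rate and direction: the test keeps about 5% and the effect is diluted. The cost is the lost power.

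A reader might go further and infer that the rule manufactures a video effect or breaks the 5% level. The Protocol does not support that as a general statement. It gives one overall loss figure and no rates by arm, it does not suggest that a clip of under a minute changes who answers the telephone, and the sign of any bias depends on which arm loses more. Unequal loss cannot be excluded, because the doctors who pass on the telephone numbers know the allocation and the blinding claim covers only the two raters. It remains a conditional risk. The t test gives higher error rates under unequal loss (about 10% at 10% v 5%, up to 27% at 10% v 0%). However, the Protocol sizes on Mann-Whitney and selects the test by distribution, and a spike of zeros would usually lead to the nonparametric test, so the Mann-Whitney figures are the relevant ones.

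The reached set is called on-treatment in Analysis strategy, while its output is headed "Per-protocol analysis for the primary outcome". This is a labelling matter: the set is defined by contact, not by receipt of the video, and it does not add to the main point.

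**Conclusion.** The rule is wrong as written for a main analysis, and it contradicts the sample-size reasoning. Under the Protocol's own assumptions (mean 10, difference 2, SD 4, 10% loss in both arms, loss unrelated to knowledge), it cuts the expected difference to about 1.8. Power at 72 per arm is about 61–65% (Mann-Whitney) or 55% (t test), against about 77–80% if reached patients are analysed. This needs no assumption of unequal loss.

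Inflation of the type I error, to about 8% or 17–18%, rests on assumed differences in loss by arm. With equal loss there is none.

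It would be a mistake to infer that the appended positive result is an artefact. Loss was small, nearly equal and slightly higher in the video arm. The rule worked against the video, and the difference remained clear (2.42, t = 3.62). That outcome does not justify the rule, which has to be sound at the 10% loss for which the trial was planned.

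**What to change.** Make the comparison of observed scores by allocated arm, now listed as secondary, the main analysis. Alternatively, keep all 144 patients with multiple imputation from variables known at discharge for everyone: centre, diagnosis, age and sex. Use education only if it is recorded at enrolment. The only place the Protocol records it is the telephone interview form, so it is missing for exactly the patients whose scores would be imputed.

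Keep score-zero as a labelled worst-case sensitivity analysis, report loss by arm, and name the reached set for what it is: observed scores by allocated arm. The allowance of 72 per arm then agrees with the analysis.

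The cost is small: wording in the Protocol and the analysis plan and a few lines of code, plus one enrolment item if education is wanted. The downside is that the main estimate then relies on scores being missing at random, an assumption that the retained zero analysis puts under stress.

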### **Statistical analyses**

Descriptive statistics will be obtained for all variables assessed in the study population. Mean and standard deviation will be used for normally distributed variables, mean and interquartile range for skewed distributions, proportions for categorical variables. Whenever relevant, 95% confidence intervals (95% CI) will be calculated.

Groups will be compared by means of parametric or nonparametric tests for quantitative variables (according to distribution; normality will be tested by means of the Shapiro–Wilk test) and Pearson’s  $\chi^2$  test (Fisher exact test where appropriate) for categorical variables. In all cases, two-tailed tests will be applied. P-value  $<0.05$  will be considered significant. Bonferroni correction will be used whenever relevant.

Factors potentially associated to knowledge and to patient’s satisfaction, including age, gender, comorbidities, years of education will be tested by means of univariate and multivariate quantile (median) regression models.

Stata computer software version 15 or higher (Stata Corporation, [name]) will be used for statistical analysis.

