### Sensitivity analysis for the primary outcome “Knowledge of the medical condition and its main complication”

| Two-sample t test with equal variances |     |           |           |           |                      |           |
|----------------------------------------|-----|-----------|-----------|-----------|----------------------|-----------|
| Group                                  | Obs | Mean      | Std. err. | Std. dev. | [95% conf. interval] |           |
| Standard                               | 72  | 6.185219  | .4036212  | 3.424839  | 5.380421             | 6.990017  |
| Video                                  | 72  | 8.705292  | .4541617  | 3.85369   | 7.799719             | 9.610865  |
| Combined                               | 144 | 7.445255  | .3205473  | 3.846567  | 6.811632             | 8.078879  |
| diff                                   |     | -2.520073 | .607596   |           | -3.721175            | -1.318971 |

diff = mean(Standard) - mean(Video)      t = -4.1476  
H0: diff = 0      Degrees of freedom = 142

Ha: diff < 0      Ha: diff != 0      Ha: diff > 0  
Pr(T < t) = 0.0000      Pr(|T| > |t|) = 0.0001      Pr(T > t) = 1.0000

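### The pooled-mean sensitivity analysis nearly repeats the completers' test with a shrunken estimate and an understated standard error, and no planned analysis lets lost patients differ by arm (minor)

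*Protocol*

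**What the plan says.** The Protocol, Analysis strategy, sets three treatments of patients lost to follow-up:

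- Main analysis: intention to treat, "considering patients lost to follow-up as having score zero".
- Secondary, on-treatment analysis: "on patients who have been reached at the follow-up call".
- Sensitivity analysis: lost patients are taken to have average knowledge, by "inputting the missing score with mean score across both groups".

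Supplementary Data 5 reports the second and third as equal-variance t tests, under titles beginning "Per-protocol analysis for the primary outcome" and "Sensitivity analysis for the primary outcome", with matching tables for therapy knowledge and satisfaction. The main-analysis table is not in the document. The Sample size section plans for 10% loss and 72 patients per arm, a 20% higher score over a control median of 10 (2 points), "with standard deviation 4 and non-normal distribution", and "alpha error 5% using a two-sided Mann-Whitney test". Under Statistical analyses, "In all cases, two-tailed tests will be applied".

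**The concern.** A sensitivity analysis for missing outcomes should show how the result moves when the assumption about the missing patients changes. A single constant computed from the patients who were reached carries no information about those who were not. Entering it as data does three things: it pulls the two arm means together, it adds observations with almost no spread, and it counts them in the sample size and degrees of freedom.

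Two things are at stake. The interval is too narrow and, if lost patients resemble their own arm, centred too close to zero. And a reader who sees the completers' and pooled-mean tables side by side may take their agreement as reassurance about loss, when most of it follows from the arithmetic.

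**Working it through.** **Inputs** (Protocol, Supplementary Data 5, primary outcome, completers). Standard: n = 69, mean 6.130435, SD 3.489114. Video: n = 68, mean 8.779412, SD 3.954388. Combined mean: 7.445255. With 72 randomised per arm, 3 Standard and 4 Video scores are missing (7/144 = 4.9%). Differences are given below as Video minus Standard.

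**Step 1: reproduce the sensitivity table.** Adding k constants c to n scores with mean m and SD s gives

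new mean = (n·m + k·c)/(n + k)

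new sum of squares = (n − 1)s² + [n·k/(n + k)](m − c)²

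- Standard: mean (69 × 6.130435 + 3 × 7.445255)/72 = 6.1852; sum of squares 832.80; SD √(832.80/71) = 3.4248.
- Video: mean (68 × 8.779412 + 4 × 7.445255)/72 = 8.7053; sum of squares 1054.42; SD √(1054.42/71) = 3.8537.
- Difference 2.5201; pooled variance (832.80 + 1054.42)/142 = 13.290; SE √(13.290 × 2/72) = 0.6076; t = 4.1476 on 142 df; 95% CI 1.319 to 3.721.

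This matches the printed table. The same rule reproduces the therapy and satisfaction tables.

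**Step 2: compare with the completers.**

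| Outcome | Completers: difference, SE, t (135 df) | Pooled mean: difference, SE, t (142 df) |
|---|---|---|
| Primary | 2.649, 0.637, 4.159 | 2.520, 0.608, 4.148 |
| Therapy knowledge | 0.281, 0.305, 0.9204 | 0.267, 0.291, 0.9205 |
| Satisfaction | 0.775, 0.557, 1.3916 | 0.737, 0.529, 1.3916 |

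Primary outcome: the difference falls by a factor 2.520/2.649 = 0.951, the share reached (137/144 = 0.951). The SE falls by 0.6076/0.6369 = 0.954. The CI width goes from 2.519 to 2.402, 4.6% narrower, with 7 more degrees of freedom and no added information.

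**Step 3: why this happens.** With the same fraction f lost in each arm of size N and completers' pooled SD s:

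- difference after filling = (1 − f) × completers' difference;
- the sum of squares hardly changes while its divisor grows, so the pooled variance is about (1 − f)s² and the SE about √[(1 − f)s² × 2/N];
- the completers' SE is √{s² × 2/[N(1 − f)]}, so the ratio of the two SEs is also about 1 − f.

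The factors cancel in t. With difference 2 and SD 4, t goes from 2.846 to 2.839 at 10% loss, and the estimate from 2.0 to 2.0 × 0.9 = 1.8. The Mann-Whitney test of the Sample size section behaves alike: simulated under the same design (3,000 trials), the correlation between the completers' z and the filled z is about 0.996 at 10% loss.

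**Step 4: comparison with other rules, primary outcome.** All are computed here from the completers' summaries.

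| Rule for the 3 + 4 missing scores | Difference | SE | t |
|---|---|---|---|
| Pooled mean (as planned) | 2.520 | 0.608 | 4.15 |
| Score zero (main analysis rule) | 2.417 | 0.667 | 3.62 |
| Multiple imputation within arm, missing at random | 2.65 | 0.639 | 4.15 |
| Worst case: Standard 18, Video 0 | 1.67 | 0.709 | 2.35 |

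The worst case has 95% CI 0.26 to 3.07 and p = 0.020.

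**Step 5: coverage and type I error.** Simulation: 20,000 trials per setting, normal scores, SD 4, 72 per arm, equal loss unrelated to the score. For a true difference of 2, coverage of the nominal 95% interval is 94.8%, 94.0% and 90.3% at 5%, 10% and 20% loss; the completers stay at about 95%. With no true difference the rejection rate is 4.6% to 5.0%, the same as for the completers.

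**The case against.** The strongest reply is that a sensitivity analysis should be judged against the main analysis, which here scores lost patients zero. Against that rule the pooled mean does change the assumption and the answer (2.520, t 4.15, against about 2.417, t 3.62), so it can expose dependence on the zero rule. This stands. A reader might infer that the analysis tests nothing at all, and the documents do not support that. What remains is that, as a test, it adds almost nothing to the completers' analysis already planned.

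Second, the shrinkage is a bias only if lost patients resemble their own arm. If those lost from both arms had the same average knowledge, as the plan's label suggests, the smaller difference is a legitimate conservative scenario. This also stands, but it does not excuse the standard error: a filled-in constant is still counted as an observed score, and the p-value is not made conservative.

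Third, multiple imputation by arm under missing at random also returns roughly the completers' result (2.65, SE 0.639, t 4.15). That is correct. It repairs the estimate and the interval; only arm-specific shifts test sensitivity.

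Fourth, the size is small, and 90% coverage needs 20% loss, twice the planned rate. That is accepted and sets the severity.

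**Conclusion.** The point holds as a minor one. The stated rule gives an understated standard error and inflated degrees of freedom and, if lost patients resemble their own arm, a difference shrunk by about the fraction lost. With similar loss in both arms its test is nearly the completers' test. Each of the three planned analyses either drops lost patients or gives both arms the same constant, so none examines loss that differs by arm in its meaning.

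Size: about 5% on estimate and SE at the 4.9% loss shown, and coverage of about 94% at the planned 10%. Type I error is not inflated. A reader might infer that the primary conclusion is in doubt; it is not, since even the most adverse filling of the missing scores leaves p = 0.020. Nor does the document claim that the agreement between the two tables proves robustness; the point is that it could not.

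The coverage figures assume normal scores and equal loss unrelated to the score. The score-zero and worst-case figures are computed from the completers' summaries.

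**What to change.** Replace the pooled-mean fill with multiple imputation by arm, combined by Rubin's rules, using variables known at enrolment for every randomised patient: centre, diagnosis, age and sex. Leave out education: the document shows it recorded only on the Telephone Interview form, which lost patients never complete.

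Use that imputation as the base for an arm-specific delta or tipping-point table. Shift the imputed scores separately in the video and control arms, keep them within 0 to 18, retain score zero as one extreme, and state the shift at which the conclusion changes.

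If the existing pooled-mean tables are kept, do not present their agreement with the completers' analysis as evidence of robustness to loss.

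The cost is a little more analysis work. No new data are needed, provided the four enrolment variables are held for all 144 patients.
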